### Analytical logic

3.8

The study design supports four complementary analytical levels:

Condition-related changes: differences in neural, autonomic, and subjective measures between mindfulness, relaxation, and control conditions.Brain–body relationships: Mechanistic analyses of coupling between neural dynamics and cardiac and respiratory rhythms across experimental phases.Interindividual variability: exploratory associations between questionnaire-based psychological and lifestyle characteristics and regulation profiles.Speech-related analyses: associations between auditory stimulus features, neural speech tracking, and exploratory acoustic features of brief post-condition verbal responses.

### Statistical analysis plan (overview)

3.9

Condition will be modeled as a within-subject factor with three levels: mindfulness/body scan, relaxation/safe place imagery, and control/podcast. The choice of statistical procedure will depend on the structure and distribution of the measures derived, for example multilevel models, parametric tests, or non-parametric tests. Repeated-measures ANOVA will be used for complete within-subject datasets when model assumptions are sufficiently met. Linear mixed-effects models will be used when appropriate to account for incomplete condition-level data, unequal numbers of usable observations, participant-level variability, or additional covariates such as condition order or medication status. If substantial deviations from model assumptions occur, for example due to pronounced non-normality, influential outliers, or distributional characteristics that are not adequately addressed by standard corrections or transformations, robust or non-parametric sensitivity analyses may be considered and explicitly reported.

#### Exploratory and mechanistic analyses

3.9.1

Mechanistic and exploratory analyses will examine neural dynamics, autonomic coupling, brain–body coupling metrics, and speech-related variables. Exploratory autonomic coupling analyses may examine associations between cardiac and respiratory dynamics, such as temporal relationships between HR, HRV, and respiration, to characterize heart–breathing coordination across conditions. These analyses will be treated as exploratory and hypothesis-generating.

Brain–body coupling analyses will include heartbeat-locked (R-peak-locked) MEG analyses, respiration-locked MEG analyses, and exploratory time-resolved coupling approaches integrating MEG, cardiac, and respiratory signals. These analyses will be used to characterize statistical dependencies between time-resolved MEG features and autonomic physiology, without making causal claims.

TRF-based neural speech tracking will be analyzed as a preregistered stimulus-engagement measure. Speech-production analyses may focus on acoustic features of brief post-condition verbal responses, such as speech rate, pause characteristics, pitch/F0, and voice quality measures, depending on recording quality and the structure of the extracted speech data. Speech-production analyses will be explicitly labeled as exploratory and interpreted accordingly. These analyses will not be interpreted as primary tests of intervention efficacy.

#### Missing data and data quality

3.9.2

Procedures for handling missing or unusable data, for example due to artifacts, will be transparently specified and reported for each outcome. Missing or unusable data will be identified using outcome-specific quality criteria, including technical recording failure, missing or corrupted channels, excessive MEG artifacts, unusable ECG or respiration signals, unreliable physiological feature extraction and physiologically implausible values. Analyses will be conducted on available data, with transparent reporting of data exclusion and sample sizes for each outcome. When condition-level data are incomplete but sufficient valid data remain for a participant, linear mixed-effects models may be used to retain these participants without requiring complete data for all conditions.

#### Multiple comparisons and inference criteria

3.9.3

Statistical significance will be evaluated using two-tailed tests with an alpha level of *p* < 0.05. For planned pairwise condition comparisons following significant omnibus tests, *p* values will be corrected using appropriate family-wise error correction procedures, such as Bonferroni or Holm-Bonferroni correction. To account for multiple comparisons across broader sets of outcomes or features, appropriate correction procedures will be applied, particularly for neural measures involving multiple frequencies, sensors, time windows, or regions of interest, for example false discovery rate (FDR) correction or cluster-based permutation approaches where applicable. Where correction procedures are not fully specified in the preregistration, the selected correction approach will be justified and transparently reported for each analysis family.

#### Program-level and clinical subgroup analyses

3.9.4

Program-level analyses will additionally compare clinical cohorts to a healthy reference cohort using mixed-effects models with condition as the within-subject factor and group as the between-subject factor; these analyses are not reported in the present study protocol. Within the clinical protocol phase, primary clinical analyses will first characterize condition effects across the combined clinical sample. Clinical subgroup analyses comparing depression and ADHD correspond to preregistered non-directional population-comparison analyses. Given feasibility constraints and the expected heterogeneity of clinical samples, these analyses will be interpreted cautiously and primarily as initial mechanistic subgroup characterizations rather than definitive diagnostic comparisons.

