### Randomization and blinding

3.3

The three auditory conditions are presented in randomized, counterbalanced order using a predefined condition-order scheme implemented in the MATLAB experiment script. Separate condition-order matrices are generated before data collection for the ADHD and depression groups using a random number generator. In the script, each auditory condition is assigned a numerical code: body scan = 1, safe place imagery = 2, and podcast = 3. These numbers are condition codes, not order numbers. For example, [1 2 3] means body scan–safe place imagery–podcast, whereas [2 3 1] means safe place imagery–podcast–body scan. In the ADHD matrix, for example, participant 1 could receive [1 2 3], participant 2 [1 3 2], and participant 3 [2 1 3]. At the start of the experiment, the experimenter enters the participant’s diagnostic group and sequential within-group participant number. The MATLAB script then selects the corresponding row from the predefined matrix and presents the audio files in that order. This procedure supports a balanced distribution of condition orders as far as possible within each diagnostic group and ensures that condition assignment is reproducible and documented. The selected order is saved in the participant log file.

No formal blinding is involved. Participants are not informed about the specific study hypotheses and will be debriefed after participation to minimize expectation-related effects.

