##### Planned sample size

3.4.2.1

Planned sample sizes are based on feasibility constraints typical for MEG studies in clinical populations and are intended to support initial mechanistic characterization rather than definitive effect size estimation. The overall clinical recruitment target is *N* = 30, with a planned minimum of *N* ≥ 15 in each diagnostic group (depressive disorders */* adult ADHD). Recruitment will continue until these targets are reached or until recruitment is no longer feasible within the project timeline.

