#### Diagnostic assessment

3.4.3

Clinical diagnoses will be established using the German clinical version of the Structured Clinical Interview for DSM-5 Disorders, Clinician Version (SCID-5-CV; Beesdo-Baum et al., 2019), conducted by trained personnel.

Current medication use is recorded for all participants, including medication type/name and dosage. This information is collected during the initial online screening and reassessed on the study day as part of the pre-experiment questionnaire to ensure accuracy and completeness. Medication use is not treated as a general exclusion criterion to reflect the clinical reality of the target populations and to support ecological validity. However, participants with recent changes in medication within the last four weeks prior to participation are excluded to reduce variability related to unstable pharmacological effects. Medication status will be considered in the statistical analyses, for example by including it as a covariate in relevant models and by conducting sensitivity analyses to assess the robustness of findings with respect to potential medication effects.

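### The outlined primary combined-sample model does not name diagnosis or condition x diagnosis, although diagnosis is fixed by design; if the two diagnoses respond differently, the standard error is overstated

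*Protocol article*

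**What the plan says.** All references are to the protocol article.

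- **Planned sample size (3.4.2.1):** "The overall clinical recruitment target is *N* = 30, with a planned minimum of *N* ≥ 15 in each diagnostic group". Diagnosis is therefore a quota.
- **Randomization and blinding (3.3):** "Separate condition-order matrices are generated before data collection for the ADHD and depression groups using a random number generator". Every participant still receives all three conditions, so diagnosis stratifies their order and not which treatment is given.
- **Statistical analysis plan, overview (3.9):** "Condition will be modeled as a within-subject factor with three levels: mindfulness/body scan, relaxation/safe place imagery, and control/podcast". Repeated-measures ANOVA is the route for complete data. Mixed models are to be used when appropriate, for reasons that include "participant-level variability, or additional covariates such as condition order or medication status".
- **Diagnostic assessment (3.4.3):** medication status is to be considered, "for example by including it as a covariate in relevant models and by conducting sensitivity analyses".
- **Program-level and clinical subgroup analyses (3.9.4):** "primary clinical analyses will first characterize condition effects across the combined clinical sample". Group as a between-subject factor is written out only for the comparison with the healthy cohort. On the two diagnoses, the section says: "Clinical subgroup analyses comparing depression and ADHD correspond to preregistered non-directional population-comparison analyses".

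**The concern.** Diagnosis is built into the design through the quota and the order matrices, and sections 2 and 3.9.4 raise the possibility of clinical heterogeneity. The outlined primary model nevertheless treats the 30 participants as one sample. If ADHD and depression respond differently to, say, body scan versus podcast, that difference is a fixed feature of a sample recruited at 15:15. A model with condition alone cannot see it as such and places it in the person-to-person error. The standard errors of the primary contrasts (ratings, HR, RMSSD, respiration rate, band power) would then be larger than the true sampling variation of the average effect. With a sample size set by feasibility, precision that can be had for one sentence of wording is worth keeping.

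**Working it through.** **Inputs from the protocol.** N = 30 and at least 15 per diagnosis, so 15 + 15 = 30 at target (3.4.2.1). Two-sided alpha 0.05, with Bonferroni or Holm as example corrections for pairwise comparisons (3.9.3). The article gives no power, effect size or SD, so there is no sample-size calculation to reproduce.

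**Assumptions.** Complete data; each person's contrast D (for example body scan minus podcast) has SD 1 within each diagnosis; delta is the ADHD-minus-depression difference in mean D. The documents give no delta, so a range is shown.

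**Step 1: main effect.** A constant added to all three conditions of every participant in one diagnosis drops out of D. Omitting a diagnosis main effect costs the contrasts nothing.

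**Step 2: interaction.** Ignoring diagnosis, the expected variance estimate is

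E[s²] = 1 + (N/(N − 1)) × delta²/4, on 29 df.

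With condition x diagnosis in the model it is 1, on 28 df. For example:

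- delta = 0.5: 1 + (30/29)(0.25/4) = 1.065
- delta = 0.8: 1 + (30/29)(0.64/4) = 1.166
- delta = 1.0: 1 + (30/29)(1/4) = 1.259

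**Step 3: interval width and power.** The width ratio is √E[s²] × t(29)/t(28) = √E[s²] × 2.045/2.048. Power is from 100,000 simulated trials per row, with the average effect set at 0.529 SD, the value that gives 80% power at N = 30.

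| delta (SD of contrast) | Variance inflation | 95% CI width, without / with term | Power without term | Power with term |
|---|---|---|---|---|
| 0 | 1.000 | 0.998 | 80.2% | 80.1% |
| 0.3 | 1.023 | 1.010 | 79.5% | 80.0% |
| 0.5 | 1.065 | 1.030 | 78.4% | 80.1% |
| 0.8 | 1.166 | 1.078 | 75.4% | 80.0% |
| 1.0 | 1.259 | 1.120 | 72.5% | 80.0% |

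At alpha 0.05/3, the strictest Bonferroni level for three pairwise comparisons (average effect 0.622 SD), power is 77.8% versus 79.9% at delta 0.5 and 70.8% versus 79.9% at delta 1.0.

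**Step 4: what does not change.** At 15:15 both models give the same point estimate, and its true sampling SD is 1/√30 = 0.183 whatever delta is. Only the estimated standard error is affected. The actual two-sided error rate falls below 5%, to about 4.4% / 3.4% / 2.9% at delta 0.5 / 0.8 / 1.0.

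**Step 5: unequal usable numbers.** An equally weighted average over diagnoses has variance (1/4)(1/n1 + 1/n2), against 1/N when the diagnoses are weighted by their observed proportions.

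- 18/12: 0.0347 against 0.0333, a penalty of 4%
- 20/10: 0.0375 against 0.0333, a penalty of 12.5%

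The choice of weights therefore matters as much as the term itself.

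**The case against.** Several counter-arguments have force.

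- **Not named is not excluded.** Section 3.9 is an overview, its covariate list is introduced by way of example, and the preregistration is not shown. A reader might infer that condition is the only term allowed, or that diagnosis has been ruled out. The text supports neither. What stands is narrower: the article does set out the factor structure and does say where group enters, and for the combined-sample analysis it does not name it.
- **Order is stratified, not assignment.** The usual rule of analysing as randomized does not by itself call for a diagnosis term here; the term tied directly to the order matrices is order, which is already listed. This is right. The better ground is the fixed quota together with possible heterogeneity of response.
- **The standard error may be the intended one.** If participants are seen as draws from a mixed clinical population, variation between diagnoses belongs in the error. But the split is set by quota and not sampled, so it adds nothing to the sampling variation of the average (step 4).
- **Diagnosis is examined anyway.** Analyses within and between diagnoses are planned, so heterogeneity is not ignored. Those separate steps do not, however, change the standard error of the combined contrast.
- **The larger figures need large differences.** True: about 0.8 to 1.0 SD. The document speaks of heterogeneity in general and gives no diagnosis-by-condition figure. It also makes no power claim, so the 80% benchmark is only a yardstick.

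**Conclusion.** The point holds as a modest, conditional one. If ADHD and depression differ in a condition contrast, a condition-only model overstates the standard error. Intervals are about 3% / 8% / 12% too wide at assumed differences of 0.5 / 0.8 / 1.0 SD, and power falls by about 2 / 5 / 7 to 8 percentage points from 80%. At 0.3 SD or less the loss is under one point, and with no difference there is none. A reader might conclude that the primary contrasts are biased, have inflated type I error or lose precision in any case. None of these follows: at 15:15 the estimate is unbiased and unchanged, and the test errs on the conservative side. The figures rest on complete data, equal within-diagnosis variances and 15 + 15 participants. This is a low-cost improvement, not a demonstrated error in the plan.

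**What to change.** In sections 3.9 and 3.9.4, state that the primary combined-sample model contains condition, diagnostic group and condition x group. A group main effect alone would recover nothing. Report the condition effect as an average over the two diagnoses with the weights stated in advance: equal at 15:15, and observed proportions where usable numbers differ by outcome, to avoid the penalty in step 5. Use the interaction from the same model for the preregistered ADHD-versus-depression comparison. Do not make inclusion depend on that interaction being significant: with 15 per group, its power is only 26% at 0.5 SD and 56% at 0.8 SD.

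The cost is a sentence or two and no new data. Each contrast loses one error df (critical t 2.045 to 2.048) and the omnibus test two (critical F 3.156 to 3.162), and the weighting has to be declared. If the preregistration already specifies this model, citing it in 3.9.4 is enough.

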## Discussion

4

### Study contribution and rationale

4.1

This study protocol specifies a standardized, within-subject experimental framework to examine acute regulation after stress induction during brief mindfulness- and relaxation-based interventions in clinical populations. By combining magnetoencephalography with cardiac activity, respiration, and repeated subjective ratings within a single session, the protocol is designed to characterize condition-related regulation across neural, autonomic, and experiential levels under tightly controlled conditions. The focus is on short, commonly used interventions delivered in a standardized auditory format, allowing differentiation between mindfulness, relaxation, and control conditions within the same individuals.

### Methodological strengths

4.2

A central strength of the protocol is the integration of multimodal measurements acquired simultaneously across conditions. This enables time-resolved analyses of neural dynamics and autonomic regulation, as well as exploratory investigation of autonomic coupling and brain–body coupling between neural oscillations and cardiac and respiratory rhythms. The within-subject design reduces interindividual confounding and supports direct condition contrasts. Standardization of auditory material, including consistent voice characteristics across conditions, is intended to minimize non-specific stimulus-related variability.

Repeated subjective stress and relaxation ratings allow experiential regulation to be assessed alongside physiological and neural measures without assuming correspondence across levels. In addition, speech-related measures provide a psychotherapy-relevant extension to the main paradigm. Neural speech tracking during auditory guidance is considered a stimulus-engagement measure, whereas speech-production features from post-condition reflections are treated as exploratory and remain methodologically constrained. Exploratory psychological and lifestyle variables are included to characterize interindividual variability and to support hypothesis generation regarding differential responsiveness. At the program level, an additional healthy reference cohort assessed with the identical paradigm will provide normative benchmarks for interpreting clinical patterns.

### Anticipated limitations and feasibility considerations

4.3

Several limitations are inherent to the proposed design. MEG recordings impose constraints on movement and overt speech, requiring rigorous artifact handling and limiting the interpretability of speech-related analyses, which are therefore treated as exploratory. Clinical populations are heterogeneous, and recruitment feasibility may constrain sample sizes, particularly for subgroup analyses. Consequently, population-level comparisons are intended to provide initial mechanistic characterization rather than definitive diagnostic differentiation. Furthermore, the single-session design focuses on acute regulatory processes and does not address longer-term intervention effects or clinical change over time.

In addition, the protocol includes a single standardized stress induction administered prior to the intervention phase, framed as a regulatory challenge to elicit a comparable initial perturbation across participants, to avoid repeated stress exposure in clinical populations and to maintain feasibility within a single-session MEG protocol. Because the stress induction occurs once and the three auditory conditions unfold afterwards in a randomized way, time-related effects such as recovery from the initial challenge, habituation, fatigue, or carryover across the session cannot be fully excluded. The block-randomized condition order is intended to reduce systematic bias by distributing such time-related effects across mindfulness, relaxation, and control conditions; however, residual carryover effects remain a consideration when interpreting condition-related differences within the acute experimental context.

### Scope of inference

4.4

This study protocol is not designed to directly evaluate the efficacy of psychotherapeutic interventions, treatment outcomes, or clinical effectiveness. Instead, all analyses are intended to characterize acute regulation within the experimental paradigm at neural, autonomic, and experiential levels, thereby providing a mechanistic description of how brief, commonly used regulatory strategies engage brain and body systems in clinical populations. Exploratory components, including autonomic as well as brain–body coupling, speech-production features, and psychological and lifestyle correlates, will be explicitly labeled as such. Brain–body coupling outcomes and TRF-based neural speech tracking will be reported according to their preregistered status. Findings will be interpreted mechanistically and descriptively, without direct causal or therapeutic claims, and will be used to generate testable hypotheses about differential responsiveness, including “what works for whom and why,” to be evaluated in future outcome-focused designs.

### Implications for future research

4.5

By providing a preregistered and transparent multimodal framework, this protocol is intended to support subsequent hypothesis-driven and intervention-focused studies that bridge mechanistic markers to psychotherapy-relevant endpoints. The design may serve as a foundation for future work, extending the acute paradigm to other psychotherapeutic intervention contexts, additional clinical populations, and personalization-oriented questions. Specifically, identifying condition-specific neural–autonomic signatures and brain–body coupling profiles may enable mechanistically informed hypotheses about individual differences in responsiveness to brief regulatory strategies.

## Ethics and dissemination

5

The study protocol has been approved by the ethics committee of the University of Salzburg (reference number: GZ41/2024 addendum). The study will be conducted in accordance with applicable local and institutional regulations. An emergency and crisis management plan is in place for acute psychological or physical distress during or after participation. Participants may pause or terminate participation at any time without negative consequences. In case of marked distress, MEG recording will be stopped immediately, and the participant will be supported by trained study personnel; if crisis indicators persist, participation will be terminated and on-site clinical staff at the Clinic will be contacted for further assessment and care. Contact information for crisis services is available in the laboratory and provided to participants as part of the study information material.

The study protocol has been preregistered on the Open Science Framework (OSF; Registration DOI: 10.17605/OSF. IO/3RHK4) to promote transparency and reproducibility. Results will be disseminated through peer-reviewed scientific publications and presentations at national and international conferences. Findings will be reported at the group level only, with a clear distinction between primary and exploratory analyses. Any deviations from the preregistered analysis plan will be transparently documented and justified in subsequent publications. Where appropriate and ethically permissible, anonymized data and analysis code may be shared in accordance with open science practices, taking particular care with respect to clinical and speech-related data. Dissemination will focus on mechanistic insights into regulation and brain–body interaction during brief mind–body interventions, providing a foundation for future hypothesis-driven and translational research rather than direct clinical recommendations.
